**Secondary Outcome Measures**

The secondary outcome measures will record the specific treatment associated quality indicators depending on the use of an EMS physician or tele-EMS physician. These specific treatment associated quality indicators are defined as:

- Quality of medical history survey (adherence to the guidelines).
- Treatment quality (adherence to the guidelines).
- Quality of documentation
- Duration of the physician engagement-time.
- Fulfillment of predefined quality indicators for "Tracer" diagnoses
- Trauma
- Stroke
- Acute coronary syndrome
- Pain control
- Bronchial asthma
- Chronic obstructive pulmonary disease (COPD)
- Seizure
- Sepsis
- Hypoglycemia
- Frequency of main diagnoses for all emergency cases
- Correct pre-hospital diagnosis (comparison to the hospital discharge diagnosis)
- AEs (independently of the kind of EMS care, e.g. allergic reaction despite adequate survey of medical history, not-intervention related blood pressure dropping, apnoea or cardiac arrest)
- Other intervention-related AEs
- Premature termination of the telemedical or conventional EMS operation, as unnecessary
- Required conversion from the primary dispatched tele-EMS physician to a conventional EMS physician
- Assessment if a conventional EMS physician operation could have been handled by a tele-EMS physician

**Other Outcome Measures**

The following variables will be assessed in each randomisation group:

- Time point of the first contact with a physician, time span between the emergency call and hospital arrival
- Seven-step National Advisory Committee for Aeronautics (NACA) severity score
- Proportion of conventional emergency cases, which were passed to a tele-EMS physician (differentiated into medical need and lack of capacity)
- Assessment if an EMS physician was necessary at all for each emergency case.
- Technical performance
- Survey of the paramedics, the patients, the EMS physicians and the emergency room personnel in regard to their satisfaction with the used EMS system.
- Death within 24 hours and until day 30 of hospitalisation, respectively until discharge from hospital
- Death within 30 and 90 days after EMS treatment
- Discharge destination from hospital
- Intensive Care Unit (ICU) and hospital length of stay
- Frequency of tele-EMS contacting by a conventional EMS physician for any kind of advice
- Assessment of the medical education/ experience of the involved physicians in each group
- All outcomes will be assessed in addition, for patients which will be recruited during the "Run-In" phase
- Retrospective analysis of the same data (excluding the prospectively collected satisfaction surveys and 30 and 90 day follow-up), like in the main study for the excluded conventional EMS physician cases. These data will be collected from the conventional EMS physician protocols and the hospital database.

**Participant timeline**

A time schedule according to the SPIRIT figure shown in Fig. 2.

**Run-In phase**

1-2 months prior to the main study, we will assess the same outcomes like in the main study.

**Phase A: Enrolment**

The dispatching personnel in the EMS dispatching centre of Aachen will screen all emergency calls for eligibility and enter a suspected diagnosis into the dispatching software.

**Phase B: Allocation**

All non-life-threatening emergency calls, which do not obligatory require an EMS physician on scene, but cannot solely be resolved by the paramedics, will be randomised into the two intervention groups (conventional EMS physician and tele-EMS physician, respectively) automatically by the dispatching software.

**Phase C: During EMS intervention, post-allocation**

Patients will be treated by both kinds of physicians according to the SOP and all operation related data will be documented in a standardised EMS documentation form according to the recommendation of the German Interdisciplinary Society for Intensive and Emergency Medicine (DIVI). As usual in the present routine, the patients in the tele-EMS physician group will be verbally informed about the use of a tele-EMS physician and the teleconsultation system. A written informed consent for study participation shall be obtained as soon as possible during this phase until discharge from hospital for all follow-up visits after the initial EMS intervention.

**Phase D: Early follow up, post-allocation**

A survey of the patients in regard to their satisfaction with the used EMS system should be conducted after hospital arrival until discharge. Assessment of the outcome death within 24 hours and until hospital discharge day, respectively. Assessment of ICU and hospital length of stay and the discharge diagnosis of the hospital.

**Phase E: Late follow up, close-out maximum until day 90**

Additionally, we will assess the mortality within 30 and 90 days, respectively.

**Phase F: Additional analysis, parallel to the main study**

Retrospective analysis of the non-randomised, with conventional EMS-physician treated patients. Satisfaction survey of the paramedics, EMS physicians and emergency room personnel.

**Sample size**

The sample size calculation is based on an assumed AE rate of 2% for the conventional physician based EMS. The rate of 2% is based on our own analysis of 100 EMS physician cases, as we could not find any information about EMS-depending AEs in the literature. We assumed a non-inferiority margin of 1.5% and allocated the overall 5% significance level to K = 3 (power (1 – β) 80.0%). Interim analysis will be performed according to the procedure of O'Brien und Flemming [28]. The critical values, power and sample sizes for the group sequential design are given in Table 1.

Using an allocation ratio of (n2/n1) = 1, the necessary sample size is 1504.2 + 1504.2 = 3008.4, thus resulting in a total sample size of 3010 patients. A fixed sample size design would need n1 = 1478.5 and n2 = 1478.5. The expected total sample size under the alternative is 2531.7. A stop for futility is not planned. Based on an expected dropout rate of 10% we aim to include 3344 patients in total (1.672 per group) in our main study.

**Recruitment**

Beside our main study, we will initially perform a 1.5-2 months "Run-In" phase, to optimise the study conduction processes. During this period, we aim to enroll, randomise and follow-up around 300-600 additional patients, which will be analysed separately from the main study. This will enable process optimisations and increase the compliance of the entire involved personnel. Thereafter, we will recruit 3344 patients, according to the sample size calculation of the main study. Patients will be recruited by the dispatching centre of Aachen. This implies the evaluation of the emergency call severity and exclusion of the life-threatening cases listed in a written procedure instruction. The impact of selection and allocation sequence bias will be determined with the type 1 error.

**Randomisation**

According to technical conditions the randomisation procedure is implemented in the software of the dispatching centre. The software is provided by the company ISE GmbH, [name], Germany. Therefore, other than initially planned, ISE and the Department of Anaesthesiology are responsible for randomisation including assessment of appropriate procedure. Details of the randomisation procedure will be described in a randomisation report, which will be kept concealed until closure of the database. The randomisation sequence will be implemented into the dispatching software and will therefore remain concealed until all important data including the suspected diagnosis of the next emergency case are entered into this system by the dispatching personnel. Following, the dispatching software will automatically randomise all patients with eligible suspected diagnoses into the two intervention groups. Hereinafter the dispatching personnel in the dispatching centre will assign the patients according to the randomisation proposal of the dispatching software.

**Blinding**

Blinding of the dispatching personnel, the paramedics on scene, patients and the physicians is not possible due to practicability reasons. Furthermore the electronic case report form (e-CRF) entering personnel cannot be blinded. The outcome assessors of the late follow-up variables and the CEC for the primary endpoint adjudication will be blinded to the kind of EMS intervention. The data safety monitoring committee (DSMC) will primarily be blinded. Only if the total number of all AEs exceeds 6%, the DSCM will not be blinded due to safety reasons.

**Un-blinding procedures**

There are no events expected to un-blind the outcome assessors.

**Data collection methods**

The entire EMS personnel (including the dispatching personnel, the physicians and the paramedics on scene) will be informed about the study procedures and supervised by the principal investigator. The principal investigator will ensure local training of the entire EMS personnel to enhance the data collection quality and reduce bias. Furthermore, the assisting study personnel will have to be adequately qualified and informed about the study protocol, any amendments, and study related responsibilities and functions. A study staff authorisation log will be maintained. Every reasonable effort will be made to follow each enrolled and randomised patient until completion of study phase E.

**Participant withdrawal and loss to follow up**

Participants may withdraw from the study for any reason at any time. The follow-up period in this study is maximum 90 days. We do not expect many withdrawals or losses to follow up until phase E. For phase E we expect a higher loss to follow up data for the outcome variable mortality on day 90. The reasons for missing data will be recorded.

**fData management**

SOP for data management will be implemented to ensure accurate, consistent, complete and reliable data. All collected data from a subject during the course of this trial have to be filled and/ or entered in the respective patient study case report form (CRF).

As source data will serve:

- The standardised routinely created EMS files on scene (during both the conventional physician as well as the tele-EMS physician operation).
- The additional EMS documentation files created in the teleconsultation centre (including the transmitted patient vital data, e.g. ECG and blood pressure measurements).
- The routinely conducted EMS operation time recording in the dispatching centre.
- Data from the admission hospital database: Diagnoses according to the 10th version of the International Classification of Diseases (ICD 10), time-points of the relevant diagnostic or therapeutic procedures (e.g. computer tomography, cardiac catheter examination), laboratory data and severity scores of diseases (e.g. National Institutes of Health Stroke Scale for stroke patients).
- The clinical follow up data like death after 24h, or 30 respectively 90 days; the ICU and hospital length of stay and the hospital discharge diagnosis, which are already collected for quality assurance reasons, based on the Law on Rescue Services of the state of North Rhine-Westphalia (RettG NRW, version of 18 March 2015); and the hospital discharge destination, will be collected from the hospital database.

A high validity of the collected data can be assumed, as they are collected during in the clinical routine and not specifically for the study. Furthermore there will not be an additional burden for the medical personnel and any acquisition and storage of sensitive and confidential patient data, as all data will be entered pseudonymised into the CRF. According to a SOP all relevant source data will be manually entered by the study personnel in a validated e-CRF form. The respective patients` paper-based CRF will contain the written informed consent with the date of subject information, a unique study and subject number.

Paper printouts of study data from an electronic database have to be signed and dated by a member of the site staff, to confirm the accuracy and completeness of data in the paper printout. Additionally, the monitor shall sign and date the verified paper printout. The paper printout shall be stored in CRF. Retrospectively entered source data information on this paper printouts have to be initiated and dated. Furthermore, any corrections of the original data require to draw a single line through the error and to sign with the date and the initials. Hereby, the crossed out entry should remain legible. The investigator shall not falsify the data.

**Clinical Endpoint Committee**

Blinded CEC members will perform the primary endpoint adjudication, to enhance the validity of the assignment of the four pre-specified AEs into intervention-related or not. The committee will consist of three members, which are fully independent from the investigators and the sponsor.

**Statistical methods**

To prove the non-inferiority hypothesis that the system-induced patient AE rate by the treatment of the tele-EMS physician compared to the conventional EMS physician is not inferior by 1.5% of the (1-α)% confidence interval for rate differences will be calculated accounted for the interim analysis (Table 1). The hybrid analysis population as developed by Sanchez will be used as analysis population [29]. Further details will be given in the trial statistical analysis plan, before database lock. The secondary dichotomous parameters will be tested by chi-square test, the continuous parameters by t-Test assuming heterogeneous variances. A subgroup analysis will be performed according to the level of medical education/ experience of the involved physicians in each group.

**Data monitoring**

This study will be conducted in accordance with the approved protocol version, the ICH-GCP (International Conference on Harmonisation of Technical Requirements for Registration of Pharmaceuticals for Human Use-good clinical practice) principles, the Declaration of Helsinki, regulatory authority requirements, and the SOP.

Qualified monitors from the sponsor Clinical Trial Centre Aachen (CTC-A) will perform the monitoring visits according to the ICH-GCP principles and their SOP. Before the initiation of this study there will be one or more monitoring visits, to check and clarify the prerequisites. The investigator is obliged to enable direct access to the source data and CRFs for study specific monitoring, auditing and inspections by the competent ethics committee. He/ she will support the respective person and be available for questions. Regular monitoring visits of random samples of data should discover and remove grievances and verify that the data collection and documentation process is conducted in concordance with the ICH-GCP principles, the study protocol and the regulatory authority requirements. The following processes and data will be reviewed in a random sample of data during the monitoring visits:

1. Entries in the e-CRF
2. Adherence to the study protocol, the ICH-GCP principles, the Declaration of Helsinki, and the regulatory authority requirements
3. Integrity of the source data and the e-CRF entries
4. Accuracy of the documentation and report of AEs and serious adverse events (SAEs) within the required time periods.
5. Patient identification, screening and enrollment log, study staff log and the monitoring log
6. Accuracy and completeness of the trial master file

Further monitoring details will be set forth in the monitoring manual.

**Data safety monitoring committee and interim analyses**

A formal DSMC will consist of three members with no competing interests and fully independent from the sponsor and investigators. Comprehensive analyses of the documented adverse events will be performed on monthly basis. They will be assessed on specific forms. The frequency of the pre-defined AEs (please see primary outcome measures) as well as non-intervention-related AEs (please see secondary outcome measures) and resuscitation within 24h of hospital admission will be referred to the safety board committee. This committee will assign, if the AEs are intervention-related or not. If there appears a difference of 5% intervention-related AEs in one study-arm, then the safety board has to recommend a prematurely study termination. Due to the complexity of the data, a useful interim analysis is planned after inclusion of 1.115 and 2.229 patients, in regard to the primary outcome variable. But if the analysis of the AEs indicates the need for an interim analysis, this will be conducted immediately.

**Harms**

We expect an increase of patient safety with the support of a tele-EMS physician in emergency cases. An intensive standardised training of the entire EMS personnel in regard to the teleconsultation system was performed already before the implementation in the routinely use. This training focused on the transmission technology and the uniform and purposeful communication. This should enable a structured, efficient and safe transmission of the conversation content. Furthermore, legal matters like the informed consent of patients, the legal relationship between the paramedics and the tele-EMS physicians and liability risks were discussed and clarified. A further safety measure is the support of the tele-EMS physicians by the software-based checklists. The advantages for checklist-based operations were shown for the patient safety within the WHO project: "Safe Surgery Saves Lifes". An improved patient outcome was shown for elective as well as emergency surgery with the checklist-based working [30-32]. The SOP for the teleconsultation system defines such checklists for the tele-EMS physicians, to ensure a necessary minimum standard of teleconsultation. E.g. intravenous drug application is only permitted if all required information is collected and all safety measures are done (like pulse oxymetry, blood pressure measurement, ECG rhythm analysis). The tele-EMS physician evaluates the validity and reliability of the teleconsultation data transfer. In cases, with low rates of data transfer and interruptions of a continuous patent monitoring, any delegation to the paramedics is not allowed according to the SOP, if a continuous monitoring is medically indicated. However, as actually nationwide usual, the paramedics would further on treat the patients, even in the case of a complete interruption of the teleconsultation system. All paramedics are educated and trained in advanced life support. Furthermore, a back up mobile phone is available in each ambulance vehicle, in accordance with German industrial standard (DIN EN 1789) and the teleconsultation centre is provided with a fixed-line connection in case of an interruption of the Internet connection. An IT-safety concept was established in collaboration with the data protection officer of the city of Aachen, to protect all transmitted and collected data against unauthorised access, unauthorised modifications and data loss. This IT-safety concept comprises also the storage time frame and the access rights.

AEs are possible in regard to technical, organisational or medical factors. Occurrence of AEs during the teleconsultation has to be documented in standardised forms provided to the tele-EMS physicians and the paramedics. These documentations have to be analysed immediately by the investigators, to recognise problems and potential hazards without time delay and to initiate countermeasures as soon as possible. AEs listed under primary outcome measures are expected in connection with the specific kind of EMS care (conventional / telemedical).

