**Survey of the personnel**

Satisfaction-survey of the paramedics, the EMS physicians and the emergency room personnel in regard to the used EMS system, will be performed with anonymised questionnaires after the EMS operation. Therefore an informed consent can be waived for these surveys.

**Table 1.** Statistical calculation based on Farrington und Manning formula [41].

| Information rate | Bounds accept H0 | Bounds reject H0 | Significance level one-sided | α spent | β spent | Power achieved | Stage n1 | Sizes n2 |
| --- | --- | --- | --- | --- | --- | --- | --- | --- |
| 0.333 | - | 3.471 | 0.0003 | 0.0003 | - | 0.0329 | 501.4 | 501.4 |
| 0.667 | - | 2.454 | 0.0071 | 0.0072 | - | 0.4424 | 501.4 | 501.4 |
| 1.0 | 2.004 | 2.004 | 0.0225 | 0.0250 | - | 0.8000 | 501.4 | 501.4 |

H0 = null hypothesis; n = number

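### Candidate primary events are recorded from richer sources in the tele arm, and no arm-neutral search is fixed before the blinded committee classifies them

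*Protocol*

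**What the plan says.** Protocol, Primary Outcome Measures, defines four intervention-related AE types and has the CEC assign reported AEs to that class under blinding. The Clinical Endpoint Committee section gives the purpose of that step as "to enhance the validity of the assignment of the four pre-specified AEs into intervention-related or not". Neither section says how candidate events are found, which records are searched, or which records the CEC receives.

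The recording sources appear in several places:

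- **Harms:** "Occurrence of AEs during the teleconsultation has to be documented in standardised forms provided to the tele-EMS physicians and the paramedics". The investigators must analyse this documentation at once. No equivalent is named for conventional missions.
- **Data management:** on-scene EMS files are listed for both kinds of mission and hospital data without restriction by arm. A further source is "The additional EMS documentation files created in the teleconsultation centre (including the transmitted patient vital data, e.g. ECG and blood pressure measurements"; no conventional counterpart is listed.
- **Teleconsultation centre:** checklist-based documentation software is used for cases with a tele-EMS physician.
- **Definition of AEs:** unexpected AEs and the expected primary-outcome AEs go on a sponsor AE form, with no limit by arm.
- **Phase C:** a standardised documentation form applies to both kinds of physician.
- **Blinding:** treating staff and e-CRF entry staff are unblinded; the CEC is blinded.

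**The concern.** Blinded adjudication protects the classification of an event that has been put forward. It cannot recover an event that nobody recorded. If the chance of being recorded differs between arms, the observed rate difference mixes true harm with detection.

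The protocol itself gives reason to expect a difference in records. Its specific secondary objective is to show superior documentation under tele, and its Discussion reports better documentation in earlier tele missions. The primary endpoint is drawn from those same records.

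The four components are not equally exposed. A blood pressure drop needing treatment and a respiratory event are on-scene events, so detection leans on the on-scene record. The allergic-reaction component turns on whether the allergy question was omitted, which is largely a matter of what was documented. Circulatory arrest within 24 hours can be sought in hospital data in either arm.

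With few expected events, a small imbalance in capture can move the result.

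**Working it through.** **Inputs from the protocol (Sample size; Table 1).** The conventional-arm rate is the "assumed AE rate of 2% for the conventional physician based EMS". The margin is stated as "We assumed a non-inferiority margin of 1.5"%, that is 1.5 percentage points. The plan "allocated the overall 5% significance level to K = 3", with 80% power and equal allocation. The final row of Table 1 reads "1.0 | 2.004 | 2.004 | 0.0225 | 0.0250": final bound 2.004, cumulative one-sided alpha 0.025. The protocol gives no capture rates; those below are assumptions, varied from 0.5 to 1.0.

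**Step 1: reproduce the plan's figures.** Farrington-Manning, with 2% in both arms:

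n per arm = [(z(1−α)·s0 + z(1−β)·s1) / δ]²

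- Restricted rates under the null: 0.02995 and 0.01495, so s0 = √(0.02995×0.97005 + 0.01495×0.98505) = 0.2092.
- s1 = √(2×0.02×0.98) = 0.1980.
- n = [(1.960×0.2092 + 0.8416×0.1980) / 0.015]², which is 1478.46 at full precision (plan: 1478.5).
- Group-sequential inflation is 1.01736, giving 1504.13 (plan: 1504.2).
- The bounds 3.471, 2.454 and 2.004 return cumulative alpha 0.0003, 0.0072 and 0.0250 and cumulative power 0.0329, 0.4425 and 0.8000, matching Table 1 to within rounding.

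The sample size is sound and is not in question. Expected events are 0.02 × 1504.2 ≈ 30 per arm.

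**Step 2: add capture.** Observed rate = true rate × capture. The Table 1 bounds and 1504.2 per arm are kept.

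Worked case: true rates 2% and 2%, tele capture 1.0, conventional capture 0.8.

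- Observed rates are 2.0% and 1.6%. The spurious excess is 0.4 points, or 0.004 × 1504.2 ≈ 6 events, and 0.4/1.5 = 27% of the margin.
- Distance to the margin: 0.015 − 0.004 = 0.011.
- Standard error at the observed rates: √[(0.02×0.98 + 0.016×0.984)/1504.2] = 0.004847. Under the null, with restricted rates 0.02752 and 0.01252, it is 0.005101.
- Final look alone: Φ(0.011/0.004847 − 2.004×0.005101/0.004847) = Φ(2.269 − 2.109) ≈ 0.56. With the two interim looks it is 0.571.

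**Step 3: the range.** In the last two columns the true tele rate is 3.5%, exactly at the margin, so declaring non-inferiority is an error.

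| Capture tele / conventional | True 2% v 2%: observed difference (points) | Power | True 3.5% v 2%: observed difference (points) | False non-inferiority |
|---|---|---|---|---|
| 1.00 / 1.00 | 0.00 | 80% | 1.50 | 2.5% |
| 1.00 / 0.95 | 0.10 | 75% | 1.60 | 1.7% |
| 1.00 / 0.90 | 0.20 | 70% | 1.70 | 1.1% |
| 1.00 / 0.80 | 0.40 | 57% | 1.90 | 0.4% |
| 1.00 / 0.70 | 0.60 | 43% | 2.10 | 0.2% |
| 1.00 / 0.50 | 1.00 | 18% | 2.50 | <0.1% |
| 0.90 / 1.00 | −0.20 | 90% | 1.15 | 8% |
| 0.80 / 1.00 | −0.40 | 96% | 0.80 | 22% |
| 0.70 / 1.00 | −0.60 | 99% | 0.45 | 46% |
| 0.50 / 1.00 | −1.00 | >99% | −0.25 | 92% |

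Fuller capture under tele costs power and lowers the risk of a false claim. Fuller capture under conventional care raises that risk.

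**The case against.** The case on the other side is substantial.

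- A reader might infer that tele-specific forms and transmitted vital data are the route by which events reach the CEC. The protocol does not say so. Harms gives those forms a purpose of their own, early recognition of hazards, and ends by saying that primary-outcome AEs are expected under either kind of care. Definition of AEs covers those events in both arms.
- A reader might infer that a conventional mission has only one observer. Background describes two paramedics plus a physician with a further paramedic, and Phase C gives both kinds of physician a standardised form.
- Electronic traces add less than they seem to. A pressure drop counts only if it needed immediate treatment, and treatment should appear on the on-scene record in either arm.
- A reader might infer that the arm difference favours a false safety claim. Fuller tele capture does the reverse. Equal under-capture does raise false non-inferiority (7.7% at 80% capture in both arms, true rates 3.5% v 2%), but that is a general property of an absolute margin, not an arm difference.
- The 2% planning rate is itself an ascertained rate, from the sponsor's review of 100 cases. The CEC's predefined criteria and the data-management SOP are not shown and may describe case-finding.

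These points rule out saying that detection does differ. They leave three things standing: the sources described are unequal, those who record and enter events are unblinded, and the protocol fixes no common search ahead of the CEC. Nor is the direction settled. A tele checklist that documents the allergy question could move tele reactions outside the endpoint definition, while an undocumented question could count against the conventional arm.

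**Conclusion.** The point holds as a credible risk of differential detection. It is not a demonstrated bias: its size is unknown and its net direction uncertain.

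The protocol describes richer recording for tele missions, and Harms and Definition of AEs are not reconciled on whether one AE form serves both arms. With about 30 expected events per arm, conventional capture at 80% of tele capture would create a 0.4-point excess and cut power from 80% to about 57%. Tele capture at 80% of conventional capture, with tele truly inferior by the full margin, would raise false non-inferiority from 2.5% to about 22%.

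These figures rest on assumed capture rates, true rates of 2% v 2% or 3.5% v 2%, 1504.2 analysed per arm, and the Table 1 bounds. They show sensitivity and do not estimate what will happen. This should be corrected in the protocol or CEC procedure, because no later analysis can restore an event that was never recorded.

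**What to change.** 1. In Harms and Definition of AEs, state that the same AE form and the same investigator review apply to conventional and tele missions.
2. In Clinical Endpoint Committee, state that candidates are identified in both arms by one fixed trigger screen of the sources that Data management lists for both: the standard on-scene EMS file and hospital data. Derive the triggers from the four endpoint definitions. Send every hit to the CEC, masked, whether or not an AE form was filed.
3. Keep all adjudicated events in the primary count, including any found only in transmitted tele data. Dropping those would remove harms from the experimental arm of a safety non-inferiority endpoint. Add a sensitivity analysis limited to events identifiable from sources common to both arms.

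The cost is protocol wording, a screening step on records already collected, and more CEC reviews, many of them negative. The protocol does not list the e-CRF fields, so whether the triggers need extra fields must be checked.
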